### Setting and recruitment

All study aims will be conducted in pediatric primary care practices affiliated with two large academic medical centers in PA. The affiliated pediatrics practices in western PA serve over 70% of youth in the region and include 32 practices across 54 office sites in nine western PA counties. This group of practices serves over 266,000 privately and publicly insured patients, aged birth to 21 years. The second affiliated primary care network in eastern PA is the largest provider of primary care services in the region, with 31 practices across five counties. Clinicians in the network serve over 249,000 private and publicly insured patients, aged birth to 21 years. For each study aim, we will obtain caregiver/guardian consent, adolescent assent and/or consent for adolescents aged 18 years.

To ensure that the participant groups (adolescents, caregivers, and primary care clinicians) across study aims are reflective of the target clinical population and implementation context, we will recruit participants as part of routine well child visits. Prior to visits, potentially eligible patients based on electronic health record (EHR) screening will receive an email jointly signed by a primary care practice champion at the family's care site and research staff providing information about the research. During well child visits, the Patient Health Questionnaire (PHQ-9-M) (81) depression screener is administered as part of standard practice and integrated into the EHR. For all study phases, we will implement EHR-based clinician-directed alerts if patient scores meet criteria for potential enrollment based on their depressive symptoms. If the patient and family are interested in the research, we will conduct either in-person or remote informed consent procedures to maximize flexibility for participants. Throughout study phases, we will monitor the recruitment of Black and/or Hispanic/Latinx adolescents and caregivers and meet regularly with primary care clinical teams to solicit ongoing feedback on recruitment procedures and adjust these methods as needed to recruit a diverse sample. The protocol for this study was approved by the Institutional Review Boards of the affiliated academic medical centers. The following sections detail additional methods by aim.

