### Aim 3: Pilot RCT of adapted TSC

#### Aim 3 participants and randomization

We will recruit 75 adolescents (at least 35% self-identifying as Black; 10% self-identifying as Latinx) to participate in the RCT comparing the adapted TSC intervention plus Sleep Feedback (TSC + Sleep Feedback, described below) to a Sleep Feedback Only condition. Study inclusion/exclusion criteria are identical to those in Aim 1. Adolescents will be eligible to enroll in the study while engaged in other behavioral/mental healthcare and/or taking any sleep medications, which we will track.

Adolescents will be randomized using 2:1 allocation (2 TSC + Sleep Feedback: 1 Sleep Feedback Only) using a modification of Efron's biased coin toss procedure (98). We selected unequal allocation to maximize critical information about the intervention (e.g., adverse events). Random assignment will balance groups on age (middle vs. high school, since school start times typically shift earlier and social pressures further shorten sleep duration in high school), suicide risk (ideation/attempt history), and racial and ethnic background.

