#### Aim 3 measures

Primary Aim 3 outcomes are related to TSC implementation, and include intervention feasibility, acceptability, appropriateness, and fidelity. Secondary Aim 3 outcomes are adolescent sleep disturbances, depressive symptoms, STB, and affective and behavioral regulation; the last of these are hypothesized intervention mechanisms (Figure 1). Sleep will be objectively assessed using actigraphy, which adolescents will wear throughout the TSC intervention period, with an accompanying daily diary to assess self-reported sleep, mood, and stressors (described below). All other secondary outcomes will be collected at baseline (pre-intervention) and at months 1, 3, 6, and 12. The type, frequency, and/or dose of behavioral, sleep, psychiatric treatment and/or medications will also be measured throughout the study using the Child and Adolescent Services Assessment (CASA) (99) throughout the study. Specific primary and secondary measures are as follows:

*Intervention acceptability* will be measured using the adolescent self-reported AIM (89) instrument, described in Aim 2. To further assess acceptability, adolescents will also complete the Client Satisfaction Questionnaire (CSQ) (100), adapted for the current study, as well as a semi-structured qualitative interview, with questions about TSC as described for the Aim 2 post-intervention interviews.

*Intervention feasibility* will be assessed through multiple methods (90), including *via* engagement (TSC sessions attended and attrition) and intervention fidelity assessments described for Aim 2. Adolescents will also complete the Intervention Appropriateness Measure (IAM) and the Feasibility of Intervention Measure (FIM) (89) to further assess perceived fit and feasibility of the intervention for addressing their sleep disturbances, respectively.

*Actigraphy* will be used to evaluate behavioral sleep and circadian characteristics, with the same procedures for implementation and scoring as in Aim 2. Outcomes for actigraphy-derived sleep disturbances are duration, regularity, and timing. Consistent with Study 1, a sleep diary will be used to complement actigraphy metrics for scoring purposes. The sleep diary will include time in and out of bed, sleep onset latency, night awakenings, and sleep quality (94). The sleep-specific diary questions will be sent *via* SMS text messages to participants each morning. See below for additional diary items administered in the evening.

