#### Aim 3 analytic approach

As Aim 3 is a pilot study, sample size considerations center on the precision of confidence interval (CI) width estimation for implementation and target outcomes. Based on best practices for pilot studies (109, 110), given our intervention sample size (TSC + Sleep Feedback) of 50 and 5% type I error rate, we will be able to estimate 95% CI widths of no more than 0.28 for primary implementation and target outcomes.

Using descriptive statistics, we will compute the proportion (and 95% confidence intervals) of participants with high ratings for TSC feasibility (session attendance >80%, attrition < 20%; FIM >80%), acceptability (AIM >80%) and appropriateness (IAM >80%). We will examine these outcomes overall and according to participant racial and ethnic groups. For implementation outcomes with both quantitative and qualitative data (feasibility, acceptability, and appropriateness), we will use established approaches for analyzing mixed methods data described as in Aim 1. We will compare participants across cells on clinical and socio-demographic baseline characteristics using standard univariate statistics.

Additionally, we will assess whether improvements in sleep (*via* actigraphy-derived duration, regularity, timing; and *via* daily diary and PROMIS measures), depressive symptoms (PHQ-9-M), and risk for STB (C-SSRS), are greater among youth randomized to TSC + Sleep Feedback vs. Sleep Feedback Only conditions using linear mixed models. Exploratory analyses will examine putative intervention mechanisms (affective/behavioral dysregulation; Figure 1) based on daily diary, CALS, and IBS ratings. Study arm, time, and their interaction will be included as primary predictors, with random effects for study subject.

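### For the questionnaire outcomes, the stated efficacy model compares change from baseline and gives month-3 intervals about 5% to 24% wider than a model with a common baseline mean

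*Protocol article*

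**What the plan says.** The Aim 3 analytic approach asks whether sleep, depressive symptoms and STB risk improve more with TSC + Sleep Feedback than with Sleep Feedback Only, using linear mixed models. The model is given in one sentence: "Study arm, time, and their interaction will be included as primary predictors, with random effects for study subject". The section does not state how time is coded, which visit carries the comparison, or whether baseline is a response or a covariate. It lists no covariates.

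The surrounding design is clear. Under Aim 3 measures, actigraphy and the daily diary run through the intervention period, and "All other secondary outcomes will be collected at baseline (pre-intervention) and at months 1, 3, 6, and 12". PROMIS, PHQ-9-M and C-SSRS fall in that second group. All efficacy outcomes are secondary; the primary outcomes concern implementation.

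Under Aim 3 participants and randomization, 75 adolescents are allocated 2:1, giving 50 versus 25; the 50 is confirmed by "given our intervention sample size (TSC + Sleep Feedback) of 50 and 5% type I error rate". Allocation is balanced on school level, "suicide risk (ideation/attempt history), and racial and ethnic background". Sessions are weekly for 6–8 weeks (Aim 2 intervention procedures, carried over under Aim 3 intervention procedures). Month 1 therefore falls during treatment, and month 3 is the first visit after it.

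**The concern.** The stated question is about improvement, and the stated terms are arm, time and their interaction. The natural reading is that baseline is one of the repeated responses and that the arm main effect is a free baseline difference. The arm-by-time term at a given visit is then the difference between arms in change from baseline. Because arms are randomised, the true baseline difference is zero, so subtracting its estimate adds noise and removes no bias. Conditioning on baseline, or giving both arms one baseline mean, uses the same data and yields a narrower interval.

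A second, conditional issue is the coding of time. A single linear slope over 12 months describes steady divergence, whereas a treatment lasting 6–8 weeks would be expected to act early.

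At stake is the precision of the efficacy estimates from a trial with only 25 controls. The Discussion says the results are meant to inform a fully powered trial.

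**Working it through.** **The plan's own figure.** The only precision figure is a 95% CI width of no more than 0.28 with n = 50. The Wald width for a proportion at p = 0.5 is 2 × 1.96 × sqrt(0.25/50) = 0.277, so it reproduces. It is a single-arm figure, does not come from the mixed model, and is unaffected by this point.

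**Inputs.** From the article: 50 versus 25, visits at months 0, 1, 3, 6 and 12, two-sided 5%. Assumed, because the article does not give them: SD = 1 at each visit, a random intercept with within-subject correlation rho from 0.3 to 0.8, complete data, categorical visits, and scores that can be treated as continuous.

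**Baseline handling.** With 1/50 + 1/25 = 0.06, the SE of the month-3 arm difference is

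- free baseline (change from baseline): sqrt(2(1 − rho) × 0.06)
- common baseline mean: sqrt((1 − rho²) × 0.06)

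The ratio is sqrt(2/(1 + rho)).

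| rho | SE free | SE common | 95% CI width free (SD) | 95% CI width common (SD) | free is wider by |
|---|---|---|---|---|---|
| 0.3 | 0.290 | 0.234 | 1.136 | 0.916 | 24% |
| 0.5 | 0.245 | 0.212 | 0.960 | 0.832 | 15% |
| 0.7 | 0.190 | 0.175 | 0.744 | 0.686 | 8% |
| 0.8 | 0.155 | 0.147 | 0.607 | 0.576 | 5% |

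For an assumed effect of 0.5 SD at rho 0.5, power is Φ(0.5/0.2449 − 1.96) = 0.53 with a free baseline and Φ(0.5/0.2121 − 1.96) = 0.65 with a common one.

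A REML simulation (150 replicates, rho 0.5, 20% dropout) gave mean SEs of 0.2547 and 0.2232, a ratio of 1.14. Mean estimates were 0.491 and 0.495 against a true 0.5, so both models recover the effect.

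**Balancing factors.** Take a time-constant factor with an assumed R² of 0.10, at rho 0.5. Added to the free-baseline model it leaves the SE at 0.2449, because it cancels from a within-subject contrast. Added to the common-baseline model it reduces the SE from 0.2121 to 0.2082, about 2%; over rho 0.8 to 0.3 the gain is about 1–3%.

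**Linear time, if it were used.** The visit times have mean 4.4 and sum of squared deviations 93.2. Suppose the true arm difference is 0, 0.5, 1, 1, 1 at the five visits (half the effect at month 1, full from month 3). The fitted slope is 6.1/93.2 = 0.0655 per month, implying 0.20 at month 3 and 0.79 at month 12, where the truth is 1 at both. If the difference instead runs 0, 0.5, 1, 0.5, 0, the slope is −2.3/93.2 = −0.025 per month, which has the wrong sign. For a sustained 0.5 SD effect at rho 0.5, the slope is 0.0327 with SE sqrt(0.5 × 0.06/93.2) = 0.0179, and power is 0.45. With categorical time none of this arises.

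**The case against.** The article condenses a fuller protocol, and calling these terms primary predictors does not exclude covariates. Time coding, target visit, covariate list and baseline handling are commonly left to the SAP. That stands: silence on them is not an error, and if baseline is in fact a covariate the loss disappears. The article does, however, state a model with an arm main effect and an arm-by-time term, and on its natural reading that model leaves precision unused.

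It is also fair that the model is unbiased, that these are secondary outcomes of a pilot, and that the month-3 interval is wide either way (0.96 or 0.83 SD at rho 0.5).

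Several stronger readings are tempting but unsupported:

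- A reader might infer that leaving out the balancing factors inflates the standard error of the interaction. It does not, since time-constant factors cancel from that contrast.
- A reader might blame lost degrees of freedom. One degree of freedom moves the t quantile only from 1.9925 (74 df) to 1.9930 (73 df); the cause is baseline noise.
- A reader might conclude that the planned contrast is misaligned with the treatment period. That follows only under linear time, which the article does not state. With categorical time the month-3 contrast is available from the model as written.
- A reader might want care network added to the allocation because recruitment is from "pediatric primary care practices affiliated with two large academic medical centers in PA". That is a preference; nothing in the article indicates a network effect.
- A reader might extend the argument to every efficacy outcome. Actigraphy and diary data are described only for the intervention period, with no pre-treatment period stated for Aim 3, so the baseline argument and a month-3 contrast are not established there.

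**Conclusion.** The point holds as a matter of efficiency, for PROMIS, PHQ-9-M and C-SSRS only. It rests on reading baseline as a response with a free arm effect, and on assumed correlations: the direction of the loss does not depend on rho, but its size does. The linear-time problem is conditional and is best treated as an ambiguity to close. Neither part makes the stated analysis invalid or touches the primary implementation outcomes.

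**What to change.** For PROMIS, PHQ-9-M and C-SSRS, replace the model sentence with wording along these lines: a linear mixed model with visit as a categorical factor; one baseline mean common to both arms (or baseline as a covariate); arm-by-visit terms at each post-baseline visit; fixed effects for school level, suicide risk, and race and ethnicity; and within-subject correlation. Report the arm difference at month 3, the first post-treatment visit, with its 95% CI, and the differences at months 6 and 12 to describe durability. The balancing factors are included mainly for consistency with the allocation.

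State a separate contrast for actigraphy and diary outcomes, defined within the intervention period.

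The cost is a change of wording and a few degrees of freedom. All the variables needed are already collected, and the randomisation procedure does not change.

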## Discussion

This paper describes a protocol for applying health equity-informed implementation science frameworks and models to adapt and evaluate the evidence-based, modularized TSC intervention in primary care with adolescents who are depressed, at risk for STB, and of primarily Black and/or Latinx backgrounds. This protocol expands upon our recent open pilot of TSC with predominantly White youth experiencing sleep disturbance and suicidal ideation, which demonstrated preliminary intervention feasibility. Minor adaptations to TSC during the pilot included integrating clinician feedback to youth on their sleep from both sleep diaries and actigraphy, and enhancing morning bright light exposure and evening blue light-blocking glasses, based on our prior research (71). Adolescents reported good adherence to these strategies on the daily diary, as well as high acceptability of these strategies, although the sample size for the post-intervention acceptability questionnaire was modest. Youth in the open pilot also showed evidence of improved 24-h rest activity rhythms.

Our planned multiphase protocol will rigorously develop and evaluate further adaptations of TSC for Black and/or Latinx youth who are treated in primary care settings. Developing adolescent behavioral healthcare that is both evidence-based and accessible is an urgent public health priority (111), particularly given the rising global prevalence of youth anxiety and depression over the course of the coronavirus (COVID-19) pandemic (112). Primary care may be a more accessible and less stigmatizing context for initiating behavioral healthcare (40, 41). The American Academy of Pediatrics also recommends routine adolescent depression screening as part of well child care (113), which facilitates early identification of youth at risk for depression and STB. Despite these benefits, substantial challenges remain to integrating behavioral health screening and referrals into the primary care workflow (114).

These challenges necessitate a CFIR-informed, pre-implementation inquiry to identify organizational and other contextual factors that are critical for intervention delivery methods and future sustainment (61, 82). Throughout the multiphase study, we will monitor whether planned implementation and research methods, such as the use of telehealth (115) and our initial focus on English-speaking families (116), inadvertently contribute to disparities in access to treatment for adolescents and their families presenting to primary care. In addition, we will measure participants' engagement in study evaluations (i.e., actigraphy and daily diaries) and the TSC intervention (i.e., session attendance), as these methods may require further adaptation to better align with the brief and less intensive nature of primary care-based service delivery. Our study will add to a growing body of research examining the feasibility and benefits of evidence-based adolescent behavioral health programs adapted for primary care delivery (117).

We anticipate that the results of the multiphase protocol will ensure adaptations to TSC are made to both optimize delivery methods for primary care and to maximize acceptability, feasibility, and effectiveness with adolescents of primarily Black and/or Latinx backgrounds. Although we have outlined potential intervention content adaptations based on relevant research (5, 9, 36, 37), any proposed cultural adaptations based on race and ethnicity are inherently limited. Race and ethnicity are socio-political constructs (118), and no racial or ethnic group is monolithic; considerable heterogeneity exists within racial and ethnic groups and along many other identity dimensions (e.g., gender identity and expression, language, religion, nationality, ability, etc.). Some of these dimensions, such as race and gender identity, may intersect to confer increased marginalization, and this intersectional lens (119) is needed to better personalize and enhance the cultural fit of any behavioral health treatment (120). Findings for the proposed research may have limited generalizability for these reasons, and due to the small proposed sample sizes across aims and the potential that only 10% of adolescent and caregiver participants may identify as Latinx and only 50% of participants may identify as Black for each aim.

Tailoring an intervention for every possible combination of intersectionality is not feasible and could further limit dissemination and uptake (121), particularly in under-resourced community settings where clinicians may not have time or access to needed trainings (47). At the same time, TSC is a modularized treatment that could facilitate attention to intersectionality with personalization (e.g., tailoring strategies to address adolescents' specific cultural and contextual sources of sleep disruption) across a range of sleep and circadian disturbances and comorbid psychiatric conditions (47). The modularized nature of TSC and the planned adaptations in this research could provide a foundation for the integration of suggested clinician and systems-level adaptations in the TSC training activities and treatment manuals, potentially overcoming the need for evaluating multiple adaptations in future research. Our qualitative, pre-implementation inquiry about TSC content and delivery strategies may also result in other adaptations that could enhance the cultural fit of other modules (e.g., integrating culture-specific beliefs around sleep in the module for correcting unhelpful sleep-related thoughts/beliefs). Indeed, we intend to use the results of this research to inform a fully-powered hybrid effectiveness-implementation trial (122) of TSC in primary care, to further establish the evidence base for TSC adaptations and to examine implementation outcomes with integrated behavioral health providers. Throughout this protocol, we may identify additional intervention content and delivery methods that require tailoring for optimal implementation and effectiveness.

Our research plan provides an example of how health equity-informed implementation science models (ADAPT-ITT) and frameworks (CFIR) can be applied to increase the likelihood that evidence-based interventions will be effective for health disparity populations and successfully implemented in accessible intervention contexts (59). Our goal is to ensure adaptations to TSC are systematically documented, rigorously tested, and developed with end-users in mind, so that this intervention can be scaled to equitably and effectively address adolescent STB.

## Data availability statement

The datasets generated and/or analyzed during the current study are not available for use outside of the University of Pittsburgh at this time, due to the nature of the ethics board approvals and possible risk(s) to study participants as well as the confidentiality promised to them. Data may be made available from the corresponding author on reasonable request with permission of study investigators and ethics board approval. Requests to access the datasets should be directed to AS, [contact].

## Ethics statement

The studies involving human participants were reviewed and approved by Institutional Review Board, School of Medicine, University of Pittsburgh, Pittsburgh, PA. Written informed consent to participate in this study was provided by the participants' legal guardian/next of kin.

